|--------------------------------------------------------------------------------------------------------|-----------------------------------------------------------------------------------------------------------------------------------------------------------------------------------------------------------------------------------------------------------------------------------------------------------------------------------------------------------------------------------------------------------------------------------------------------------------------------------------------------------------------------------------------------------------------------------------------------------------------------------------------------------------------------------------------------------------------------------------------------|---------------------------|---------------------------|
| Protocol versions with all changes marked in yellow between versions are kept in the Trial Master File |                                                                                                                                                                                                                                                                                                                                                                                                                                                                                                                                                                                                                                                                                                                                                     |                           |                           |
| v. 1.0
22.04.2020                                                                                   | - Original protocol submission                                                                                                                                                                                                                                                                                                                                                                                                                                                                                                                                                                                                                                                                                                                      | Not submitted             | Not approved              |
| v. 1.1
29.04.2020                                                                                   | 
Changes made relating to:
 
 
• Description of unblinding
 
• Pre-specification of primary end-point analysis and stratification
 
• Specifications regarding statistical populations between ITT and FAS
 
• Specifications regarding final Covid-19 diagnosis as statistical sub-group
 
• Confirmation that all women of less than 50 years of age will be asked about possible pregnancy
 
• stop-criteria for the IMP administration is updated.
 
• Medical oxygen has been defined as non-IMP in updated protocol
 
• Statement regarding the use of IMP within MA is updated
 
• Specification to exclusion criterion number 8
 
 |                           |                           |

## LIST OF ABBREVIATIONS AND DEFINITIONS OF TERMS

| Abbreviation or special term | Explanation                                                                                                                                                                                                                                                                                     |
|------------------------------|-------------------------------------------------------------------------------------------------------------------------------------------------------------------------------------------------------------------------------------------------------------------------------------------------|
| AE                           | Adverse Event                                                                                                                                                                                                                                                                                   |
| AMIS                         | Computer registry at AMK                                                                                                                                                                                                                                                                        |
| AMK                          | Emergency Medical Dispatch Centre                                                                                                                                                                                                                                                               |
| ARDS                         | Acute respiratory distress syndrome                                                                                                                                                                                                                                                             |
| COVID-19                     | Disease caused by SARS-CoV-2 coronavirus                                                                                                                                                                                                                                                        |
| CRF                          | Case Report Form (electronic/paper)                                                                                                                                                                                                                                                             |
| CSA                          | Clinical Study Agreement                                                                                                                                                                                                                                                                        |
| CTC                          | Common Toxicity Criteria                                                                                                                                                                                                                                                                        |
| CTCAE                        | Common Terminology Criteria for Adverse Event                                                                                                                                                                                                                                                   |
| DAE                          | Discontinuation due to Adverse Event                                                                                                                                                                                                                                                            |
| DMC                          | Data monitoring committee                                                                                                                                                                                                                                                                       |
| EC                           | Ethics Committee, synonymous to Institutional Review Board (IRB) and Independent Ethics Committee (IEC)                                                                                                                                                                                         |
| ECG                          | Electrocardiogram                                                                                                                                                                                                                                                                               |
| EOI                          | End of intervention                                                                                                                                                                                                                                                                             |
| EPJ                          | Electronic Patient Journal                                                                                                                                                                                                                                                                      |
| EtCO 2            | The amount of carbon dioxide (CO 2 ) in exhaled air                                                                                                                                                                                                                                  |
| GCP                          | Good Clinical Practice                                                                                                                                                                                                                                                                          |
| IB                           | Investigator's Brochure                                                                                                                                                                                                                                                                         |
| ICF                          | Informed Consent Form                                                                                                                                                                                                                                                                           |
| ICH                          | International Conference on Harmonization                                                                                                                                                                                                                                                       |
| IMP                          | Investigational medicinal product                                                                                                                                                                                                                                                               |
| INO                          | Inhaled Nitric Oxide                                                                                                                                                                                                                                                                            |
| KDIGO                        | Kidney Disease Improving Global Outcomes (KDIGO)                                                                                                                                                                                                                                                |
| LABAS                        | Electronic patient journal in OUH Air Ambulance Service                                                                                                                                                                                                                                         |
| Norcrin                      | Norwegian Clinical Research Infrastructure Network                                                                                                                                                                                                                                              |
| OUH                          | Oslo University Hospital                                                                                                                                                                                                                                                                        |
| OUH                          | Oslo University Hospital                                                                                                                                                                                                                                                                        |
| PEEP                         | Positive end-expiratory pressure                                                                                                                                                                                                                                                                |
| ppm                          | Parts per million                                                                                                                                                                                                                                                                               |
| RSI                          | Rapid Sequence Induction                                                                                                                                                                                                                                                                        |
| SAE                          | Serious Adverse Event                                                                                                                                                                                                                                                                           |
| SARI                         | Severe acute respiratory infection                                                                                                                                                                                                                                                              |
| SARS-CoV-2                   | Novel coronavirus causing covid-19 disease                                                                                                                                                                                                                                                      |
| SOP                          | Standard Operating Procedure                                                                                                                                                                                                                                                                    |
| SPC                          | Summary of product characteristics                                                                                                                                                                                                                                                              |
| SpO 2             | Oxygen saturation                                                                                                                                                                                                                                                                               |
| SUSAR                        | Suspected Unexpected serious adverse reaction                                                                                                                                                                                                                                                   |
| TMF                          | Trial master file                                                                                                                                                                                                                                                                               |
| V/Q ratio                    | V – ventilation – the air that reaches the alveoli
Q – perfusion – the blood that reaches the alveoli via the capillaries
The V/Q ratio can therefore be defined as the ratio of the amount of air reaching the alveoli per minute to the amount of blood reaching the alveoli per minute |
| WHO                          | The World Health Organization                                                                                                                                                                                                                                                                   |

# 1 INTRODUCTION

## 1.1 Background

### **SARS-CoV-2 and COVID-19 epidemiology**

In December 2019, several unexplained viral pneumonia cases occurred in Wuhan, China. Etiological research conducted identified what was later to be named the severe acute respiratory syndrome coronavirus 2 (SARS-CoV-2). The World Health Organization formally named the disease triggered by SARS-CoV-2 the coronavirus disease (COVID-19) (1). In March 2020, WHO announced the COVID-19 a pandemic and a major global public health emergency(2). Mortality from COVID-19 is rapidly increasing in Europe and the USA, with acute respiratory failure as the predominant cause of death(3).

#### **1.1.1 WHO Case definitions for surveillance of covid-19:**

##### Suspected case

A. A patient with acute respiratory illness (fever and at least one sign/symptom of respiratory disease, e.g., cough, shortness of breath), AND a history of travel to or residence in a location reporting community transmission of COVID-19 disease during the 14 days prior to symptom onset;

OR

B. A patient with any acute respiratory illness AND having been in contact with a confirmed or probable COVID-19 case (see definition of contact) in the last 14 days prior to symptom onset;

OR

C. A patient with severe acute respiratory illness (fever and at least one sign/symptom of respiratory disease, e.g., cough, shortness of breath; AND requiring hospitalization) AND in the absence of an alternative diagnosis that fully explains the clinical presentation.

##### Probable case

A. A suspect case for whom testing for the COVID-19 virus is inconclusive.

OR

B. A suspect case for whom testing could not be performed for any reason.

##### Confirmed case

A person with laboratory confirmation of COVID-19 infection, irrespective of clinical signs and symptoms.

#### **1.1.2 Clinical Aspects and Pre-hospital Considerations**

COVID-19 is characterized by an initial phase of unspecific symptoms. Due to risk of disease transmission, patients are generally advised to stay at home, unless medical care is needed. A significant proportion of these cases develop critical respiratory failure so rapidly that initial emergency medical management is required in the pre-hospital phase.

Already during the initial phase of the outbreak in Norway, Oslo University Air Ambulance Department encountered patients with life threatening respiratory failure, resembling a clinical picture similar to acute respiratory distress syndrome (ARDS), with severe hypoxia. The WHO also reports similar clinical picture in covid-19 patients, with rapidly progressive life-threatening respiratory failure. The WHO recommendations laid

out 13th March 2020 form the basis of the present trial protocol and is found as an appendix.

- **Management of severe COVID-19: oxygen therapy and monitoring:**

Give supplemental oxygen therapy immediately to patients with SARI and respiratory distress, hypoxaemia or shock, and target SpO2 > 94%.

Remarks for adults: Adults with emergency signs (obstructed or absent breathing, severe respiratory distress, central cyanosis, shock, coma or convulsions) should receive airway management and oxygen therapy during resuscitation to target SpO2 ≥ 94%. Initiate oxygen therapy at 5 L/min and titrate flow rates to reach target SpO2 ≥ 93% during resuscitation; or use face mask with reservoir bag (at 10–15 L/min) if patient in critical condition

- **Management of critical COVID-19: ARDS**

Recognize severe hypoxemic respiratory failure when a patient with respiratory distress is failing to respond to standard oxygen therapy and prepare to provide advanced oxygen/ventilatory support.

Remarks: Patients may continue to have increased work of breathing or hypoxemia even when oxygen is delivered via a face mask with reservoir bag (flow rates of 10–15 L/min, which is typically the minimum flow required to maintain bag inflation; FiO2 0.60–0.95). Hypoxemic respiratory failure in ARDS commonly results from intrapulmonary ventilation-perfusion mismatch or shunt and usually requires mechanical ventilation.

Endotracheal intubation should be performed by a trained and experienced provider using airborne precautions.

Remarks: Patients with ARDS, especially young children or those who are obese or pregnant, may desaturate quickly during intubation. Pre-oxygenate with 100% FiO2 for 5 minutes, via a face mask with reservoir bag, bag-valve mask, HFNO or NIV. Rapid-sequence intubation is appropriate after an airway assessment that identifies no signs of difficult intubation.

As stated above, patients in severe respiratory failure will require mechanical ventilation. Mechanical ventilation is artificial ventilation where spontaneous breathing is replaced with a machine (ventilator/ respirator/ re-inflatable bag) breathing into the patients' lung via an endotracheal tube. The placing of an endotracheal tube in emergency settings, as opposed to elective, is referred to as Rapid Sequence Intubation (RSI). To achieve intubation and mechanical ventilation the patient needs to be anesthetized.

In order to perform an RSI and endotracheal intubation, the patients need preoxygenation. The procedure itself is a high-risk medical intervention, particularly when the indication for RSI is expiratory failure and hypoxaemia.

To increase the safety margins preoxygenation by applying a closed facemask with high flow oxygen and positive end-expiratory pressure (PEEP). Intubation follows standard guidelines in the service that describe equipment and drugs used for the procedure.

## 1.2 Background - Therapeutic Information and clinical experience

### 1.2.1 Standard prehospital treatment in respiratory failure

Respiratory failure is a common presentation in emergency medicine, and its treatment is both aimed at identifying and treating the cause of the problem, and immediate symptomatic treatment. Intervention follows the basic algorithm common to all emergency medicine: A, B, C; meaning Airway, Breathing, Circulation; with interventions falling under each category and the order for these interventions going from A through to C.

**Airway:** this means securing the patients has a free and unobstructed airway from the mouth and down through the pharynx and trachea into the lungs. Interventions under A include removing foreign objects, chin- and jaw lift to avoid the base of the tongue blocking the airway, insertion of a Guedel- airway or endotracheal intubation. The endotracheal intubation is considered a “secure- airway” and is often part of physician-manned emergency care and prior to transport. There may be instances where the intubation is delayed until arrival at the hospital and the treating emergency doctor chooses to bag- mask ventilate the patient outside of the hospital and during transport.

**Breathing:** Interventions under B includes the administration of oxygen, either via face masks and nasal prongs in patients with spontaneous respiration, or via bag- mask ventilation of more invasive airway devices such as intubation. Mechanical ventilation is included under this point.

**Circulation:** Intervention under this point includes the administering of IV fluids, transfusion, medication for blood pressure such as adrenalin, noradrenalin or others.

For endotracheal intubation most patients, require deep sedation and muscle relaxation- the induction of anaesthesia. Common drugs to obtain this is ketamine or propofol for sedation and suxamethonium or rocuronium bromide for relaxation. These drugs may be administered IV or interosseous, rarely intramuscularly. For the safest possible intubation, a period of preoxygenation must occur. This involves saturating the patient's lungs and blood stream with oxygen, and the intubation invariably induces a short time period where the patient is apnoeic. During this time patients may have a considerable drop in their SpO2, especially if they are critically ill. This is a central rationale for the present trial, to increase the oxygen uptake during this preoxygenation phase.

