|   |                                                                                                                                                                                        |                          | 1.2.7     | Cardiac arrest during intervention                            | Utstein definition (13)                                                       |  |
|   |                                                                                                                                                                                        |                          | 1.2.8     | GOS-E score on day 28                                         | GOS-E: Glasgow Outcome Score Extended                                         |  |
|   |                                                                                                                                                                                        | 1.2.9                    | Mortality | 24 hour and 28 days                                           |                                                                               |  |
|   | Secondary                                                                                                                                                                              |                          |           | Secondary                                                     |                                                                               |  |
| 2 | Evaluate the safety of the intervention as compared to the control as assed by:                                                                                                        | 2.1 Circulatory function | 2.1.1     | Heart rate at $t_0\text{-}t_n$                                | Actual HR at time point                                                       |  |
|   |                                                                                                                                                                                        |                          | 2.1.2     | Blood pressure at $t_0$ to $t_n$                              | Invasive or non-invasive. Actual BP at time point                             |  |

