## 5.5 Concomitant Medication

### Non- IMP to all patients in this trial:

**Medical oxygen** (ATC: V03AN01) Medicinal gas, compressed. Current Trade Name: Conoxia 100 % . Oxygen will be delivered using standard and non-modified equipment, and connected to INOBlender as shown in 5.3.1. It will be delivered at a rate of 10 Litre/ minute. Please see attached SPC (in Norwegian)

- No medication excludes participants from being included in this trial.
- Medical oxygen will be delivered to all patients included in this trial.
- Medications used by patients prior to acute illness and inclusion in this trial will be recorded if information is available at the time of inclusion.
- All medications administered as part of emergency treatment and intubation will be recorded in the CRF. It is expected that patient will be treated with sedatives such and ketamine or propofol, opioids such as fentanyl and neuromuscular blockers such as rocuronium bromide. Medications will be recorded as ATC number, generic name, dose and route of administration. The list below is an example of the most common medications used, this is not exhaustive. A search at [interaksjoner.no](http://interaksjoner.no) between these listed medications with R07A X01 Nitrogenoksid does not yield any interactions. That search also informs us that the database is not updated. The SmPC does states some caution with concomitant use of prilocaine, a local anesthetic not used in emergency medicine. This is a very unlikely happening, and if co-administered will be noted in the CRF.

| Common medication in Air Ambulance setup (In Norwegian) |                                |
|---------------------------------------------------------|--------------------------------|
| Adenosin life inf/inj 5mg/ml                            | Lidokain mylan inj 20mg/ml     |
| Adrenalin base NAF injkons 1mg                          | Magnesiumsulfat inf kons 1mmol |
| Adrenalin takeda inj 0,1mg/ml                           | Metalyse inj subst 10000U      |
| Adrenalin takeda inj 1mg/ml                             | Midazolam braun inf/inj 1mg/ml |
| Aminophylline amd inj 25mg/ml                           | Na kl braun inf 9mg/ml Eco+    |
| Amiodaron ham inf/inj kon 50mg                          | Na kl braun infkon 1mmol/ml MP |
| Aspirin inf/inj subst 500mg                             | Na kl fres t par br 9mg/ml pl  |
| Atropin takeda inj 1mg/ml                               | Naloxon hamel inf/inj 0,4mg/ml |

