#### Secondary objectives

The endpoints of the secondary objectives reflect the known adverse effects of INO. Although this are not described after short-term administration, they will be included in this study. Both bradycardia and hypotension are possible side effects of NO. Both heart rate and blood pressure will be monitored during the intervention phase, and samples every 5 minutes are used as endpoints. (2.1.1 and 2.1.2)

All other secondary outcome parameters are collected from the patient journal.

Acute kidney injury is classified in three stages according to KDIGO. (2.2.2) A more sensitive but less specific marker of kidney function is the change in serum urea concentration. (2.2.1). Both measures are gathered on the 28-day follow-up, and the value most strongly indicative of kidney failure is used for this endpoint. Platelet count, Methaemoglobinaemia is collected from the patients EPJ.

Data from patient monitor measuring impedance (ohms) will be used to calculate respiratory rate.

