| Vascular disorders                              | 
 
• Acute hypotension
 
                                                                                                                                                                                                  |

Please note: Both suspected rebound reactions and death prior to end of intervention will always be reported to Sponsor as a serious adverse event.

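### The blood pressure and heart rate endpoints take values as they stand after any circulatory drug, so a treated fall is understated in the between-arm safety comparison

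*Protocol*

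**What the plan says.** Protocol Section 2 places circulatory function under the safety objective and defines the two endpoints as "Actual HR at time point" (2.1.1) and, for blood pressure (2.1.2), "Invasive or non-invasive. Actual BP at time point". Section 7.1.2 gives the reason: "Both bradycardia and hypotension are possible side effects of NO". It adds: "Both heart rate and blood pressure will be monitored during the intervention phase, and samples every 5 minutes are used as endpoints".

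Section 1.2.1, describing standard prehospital care under the heading Circulation, says: "Intervention under this point includes the administering of IV fluids, transfusion, medication for blood pressure such as adrenalin, noradrenalin or others". Section 5.5 bars no drug at inclusion ("No medication excludes participants from being included in this trial"), and its list of drugs carried by the service includes adrenaline, noradrenaline, ephedrine, atropine and isoprenaline. The same section says "All medications administered as part of emergency treatment and intubation will be recorded in the CRF", naming ATC number, generic name, dose and route as the fields.

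Section 10.5 analyses continuous secondary endpoints like the primary one and/or by repeated measures mixed models. No endpoint in Section 2 counts circulatory drugs, and Section 10.5 does not mention them.

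**The concern.** A vasopressor given after allocation is partly a consequence of the harm these endpoints are meant to detect. If nitric oxide lowers the pressure in more patients, more of them are likely to be treated, and their later readings move back towards those of the control arm. The contrast in actual pressure then shrinks, and for a safety endpoint this is the unsafe direction. More frequent sampling would not cure it, because the treated pressure itself has been changed.

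At stake is how a null result on 2.1.2 is read. It could mean that the circulation was unaffected, or that it was affected and supported. The endpoint as defined cannot separate the two.

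**Working it through.** **The protocol's own figure.** Section 10.1 gives SD 10, within-subject correlation 0.8, difference 5 points, power 80% and significance level 5% (two-sided assumed).
- SD of change = √(2 × 10² × (1 − 0.8)) = 6.32, as stated.
- A two-sample t-test has power 0.798 at 26 per arm and 0.813 at 27. So 27 per arm (54) reproduces. It is used below as the size at which the pressure endpoint would be compared.

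**Inputs that the protocol does not give.** It states no SD, effect, treatment trigger or target for blood pressure. All mmHg figures below are assumptions for illustration, and the trigger values are not proposals for care.

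**Step 1: part of the mean difference undone.** Observed difference = D × (1 − f), where f is the share undone by drugs. With D = 15, SD = 20, 27 per arm, two-sided 5%:

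| f | observed difference (mmHg) | power |
|---|---|---|
| 0 | 15 | 0.77 |
| 0.25 | 11.25 | 0.53 |
| 0.50 | 7.5 | 0.27 |
| 0.75 | 3.75 | 0.10 |
| 1 | 0 | 0.05 |

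Over SD 15–25 and D 10–20, untreated power is 0.30–1.00. It becomes 0.11–0.67 with half undone and 0.05 with all undone.

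**Step 2: only patients below a trigger are treated.** Control mean 120, nitric oxide mean 105, SD 20. All or half of those below the trigger receive a drug and are reset to a target (20,000 simulated trials per case):

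| trigger / target | share treated | observed difference (mmHg) | power | drug use, control vs nitric oxide |
|---|---|---|---|---|
| 90 / 110 | half | 12.3 | 0.70 | 3% vs 11% |
| 90 / 110 | all | 9.8 | 0.63 | 7% vs 23% |
| 100 / 110 | half | 11.8 | 0.69 | 8% vs 20% |
| 100 / 110 | all | 8.5 | 0.63 | 16% vs 40% |
| 100 / 120 | half | 10.6 | 0.59 | 8% vs 20% |
| 100 / 120 | all | 6.1 | 0.41 | 16% vs 40% |

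The difference is diluted in every case and removed in none. Drug use separates the arms.

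**Step 3: what a combined count does.** Take the event as a pressure below the limit or a drug given, with the limit set equal to the trigger.
- Limit 100: Φ((100 − 120)/20) = Φ(−1) = 16% on control; Φ((100 − 105)/20) = Φ(−0.25) = 40% on nitric oxide.
- Limit 90: Φ(−1.5) = 7% and Φ(−0.75) = 23%.

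These shares do not change with how many falls are treated, provided the untreated falls are seen at a reading. The count is not powerful, however. For an assumed 30% against 10%, Fisher's exact test has power of about 0.31 at 27 per arm.

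**The case against.** The strongest reply is that the trial records these harms elsewhere. Section 8.2.2 lists bradycardia and "Acute hypotension" among the expected serious events entered in the CRF. Section 8.3 collects adverse events from allocation to end of intervention and asks for the listed serious ones at day 28. Section 8.4 records the action taken, and Section 8.5.3 puts events into the study report. This stands as partial mitigation: a treated fall need not be lost to the trial. But these sections state no pressure or heart rate limit, so recording rests on judgement, and Section 10.5 names no comparison of these events by arm.

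A second reply is that actual pressure under usual care is a legitimate treatment-policy measure, and that handling of rescue drugs belongs in the SAP. The first half is right, which is why the endpoints should stay. On the second, an SAP can set sensitivity analyses, but a count of treated falls adds to what Section 2 fixes as the circulatory endpoints.

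A reader might also infer that a falling pressure is treated at once and that harm will therefore show as no difference. The documents do not support this. Section 1.2.1 is background, with no trigger or timing, and the drugs that Section 5.5 expects are sedatives, opioids and neuromuscular blockers. Complete masking is only the limiting case. Nor does Section 1.2.1 cover heart rate: its sentence concerns drugs for blood pressure, and only the service's general drug list points to treatment of bradycardia.

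**Conclusion.** The point holds as dilution. Section 2 fixes endpoint 2.1.2 as the pressure actually measured, circulatory drugs may be given during the intervention, and neither Section 2 nor Section 10.5 uses the drug record. A treated fall is therefore understated between arms. For heart rate (2.1.1) the same mechanism is possible but less well supported.

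Under the assumed 15 mmHg fall, SD 20 and treatment below a trigger, 6.1–12.3 mmHg of the difference remains. The direction follows from the design if drugs are given in response to a fall. The size rests wholly on assumed values. This concerns a secondary safety objective, is partly offset by event recording, and is worth correcting because most of the data needed are already planned.

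**What to change.** Keep actual heart rate and blood pressure as 2.1.1 and 2.1.2. Beside them, in Sections 2 and 10.5, add:

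- the number of patients by arm, from allocation to end of intervention, with either a blood pressure (for 2.1.1, heart rate) below a limit the sponsor prespecifies, or a vasoactive (for 2.1.1, anti-bradycardia) drug given, with exact intervals;
- a table of these drugs by arm.

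The sources are the patient monitor and the CRF medication record. The window fits the planned recording: Section 5.4.1 records drugs given before the study drug, and Section 5.5 stops recording at end of intervention.

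Split the count before and after induction only if the CRF captures administration time, which Section 5.5 does not list; otherwise a time field has to be added. Any model that omits readings after rescue conditions on a post-randomisation event and should be labelled exploratory.

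The cost is endpoint and analysis wording, handled as a protocol amendment under Section 11.4, plus the time field if the split is wanted. Some drug use will be for induction rather than for an effect of nitric oxide. Power is low at 27 per arm, so the count should be read through its interval, not as a test of safety.
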